## Introduction

Preeclampsia is a progressive multisystemic complication of pregnancy characterized by hypertension and often proteinuria, typically occurring after 20 weeks of gestation [1]. It affects approximately 2–8% of pregnancies globally [2] and up to 16.7% among pregnant women in Nigeria [3]. Preeclampsia remains a leading cause of maternal and perinatal morbidity and mortality worldwide, particularly in low- and middle-income countries [4]. Preeclampsia with severe features represents an escalation of preeclampsia severity and is associated with a higher risk of adverse maternal and fetal outcomes [2,5]. Severe features of preeclampsia include a systolic blood pressure of at least 160 mmHg or a diastolic blood pressure of at least 110 mmHg, thrombocytopenia, impaired liver function, severe persistent right upper quadrant pain, progressive renal insufficiency, pulmonary oedema, and new-onset cerebral or visual disturbances [6].

Despite significant advancements in obstetric care, the incidence of preeclampsia remains a substantial public health challenge [7] and effective strategies to prevent the disease progression remain limited, particularly in low-resource settings. While certain interventions, such as low-dose aspirin prophylaxis [8] in high-risk women, have shown some efficacy in reducing the risk of preeclampsia, there remains a need for additional measures to prevent the development of severe disease in women with early-onset preeclampsia, particularly in resource-constrained settings where the burden of disease is greatest [4]. Currently, the only cure for preeclampsia is delivery of the fetus and placenta [7,9] however, this is commonly associated with iatrogenic preterm delivery. To prevent this complication and improve maternal and perinatal outcomes, research efforts are currently focused not only on the prevention of preeclampsia but also on its treatment and prevention of its severe features.

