### Study outcomes

The primary outcome measure was time-to-disease progression (in days) among women with early-onset preeclampsia, defined as the interval from diagnosis to the first occurrence of a composite endpoint indicating clinical deterioration. Disease progression is defined as the development of any of the following: consistently elevated blood pressure of 160/110 mmHg or higher; severe proteinuria of 3+ or a urine protein/creatinine ratio of 0.3 or higher; platelet counts less than 100,000/µL; elevated liver enzymes (AST/ALT) or evidence of hepatic dysfunction; serum creatinine level greater than 1.1 mg/dL or doubling of baseline creatinine in the absence of other renal diseases; symptoms and signs of pulmonary oedema such as dyspnoea and crackles on lung auscultation; cerebral or visual disturbances such as headaches, visual disturbances, altered mental status, seizures (eclampsia), or other neurological symptoms; and evidence of placental dysfunction such as placental abruption, fetal growth restriction or oligohydramnios on ultrasound examination [2,5]. Participants who do not experience disease progression will be censored at delivery or at the end of follow-up. Secondary outcomes will include (1) safety and treatment tolerability, (2) maternal outcome (maternal mortality), and (3) composite neonatal outcomes, including low birth weight in term neonates (baby’s birth weight less than 2500g), IUGR, stillbirth, NICU admission, and perinatal and neonatal mortality. Women who develop preeclampsia with severe features will be managed as per the obstetric unit protocol and will be excluded from further participation in the study.

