### Sample size calculation

The sample size was calculated assuming a 1:1 randomization ratio, a two-sided type I error rate (α) of 0.05, and 80% statistical power to detect a hazard ratio of 0.5 between the NAC and placebo groups, based on an estimated 33.3% baseline probability of disease progression among pregnant women with early-onset preeclampsia [24]. Allowing for an anticipated 15% loss to follow-up or missing outcome data, the total planned sample size is 153 participants, who will be randomly allocated in equal proportions to the two study arms (approximately 76–77 participants per group).

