
**Fig 1 pone.0347695.g001:**
[figure not shown]
Trial flow chart.

**Follow-up evaluations:** Data collection will commence on the day the participant is randomized into the trial and will continue until the trial is terminated or the participant withdraws from the trial at any time for any reason. Study visits will be scheduled every two weeks until 32 weeks and weekly thereafter until delivery [Table 1]. Participants will be monitored using a daily symptom diary to record features of severity—headaches, visual disturbances (e.g., blurred vision, scotoma), dyspnoea, and right hypochondria or epigastric pain and any adverse event—gastrointestinal upset, dry mouth, nausea, vomiting, diarrhoea, rash, and fatigue and its severity using a daily symptom diary and present this for recording at their next clinic visit. At every follow-up visit, a newly filled dispensing sachet containing the experimental drugs with the same numeric code will be given to each woman, and the pills remaining in used sachets are then counted to assess adherence. Adherence will be defined as the use of at least 70% of the prescribed tablets for each participant. Allocations to treatment arms will be concealed from the study investigators, clinic staff, and trial statistician using sealed opaque envelopes that are sequentially numbered. The onsite pharmacy technicians will not be involved in the design, conduct, statistical analysis, and reporting of study findings. Additional information to be collected during the follow-up visits includes a history of allergies, level of treatment adherence, drug tolerability, bedside urinalysis for albumin, venous blood samples for biweekly measurements of haemoglobin, creatinine, liver enzymes (AST/ALT), and complete blood count. Serum biochemical assessments of glutathione and homocysteine levels will be performed at randomisation (baseline) and at weeks 28 and 32. Fetal growth scans and umbilical artery velocimetry (from 32 weeks) will also be done biweekly until delivery. At delivery, data on gestational age (in weeks), total duration of experimental drug intake (in days), intrauterine growth restriction (IUGR), neonatal birth weight (in grams), neonatal status at birth, 7th- and 28th-day (dead/alive), neonatal intensive care unit (NICU) admission, and length of NICU admission (in days) will be collected and recorded in the electronic CRF. Cord blood sampling at delivery for analysis of glutathione and homocysteine levels will also be collected to provide additional insight into maternal-fetal antioxidant transfer and potential downstream effects of NAC [Table 1].

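### Death is the only maternal efficacy outcome among the secondaries and 153 women cannot inform it; gestational age at delivery is recorded but is not an outcome, so no prespecified outcome tests whether delayed progression prolongs pregnancy

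*Protocol article*

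**What the plan says.** Study outcomes gives a numbered list of three secondary outcomes: safety and tolerability, then "2) maternal outcome (maternal mortality"), then a neonatal composite. The neonatal list covers low birth weight in term babies, growth restriction, stillbirth, NICU admission, and perinatal and neonatal death. Gestational age at delivery, preterm birth and prolongation of pregnancy are not on it.

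The follow-up text collects the relevant variable: "At delivery, data on gestational age (in weeks), total duration of experimental drug intake (in days"), with further items, go into the electronic CRF.

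The Introduction calls delivery the only cure and says that "this is commonly associated with iatrogenic preterm delivery". It then describes research that aims to prevent this complication and to improve maternal and perinatal outcomes.

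Three further statements matter:
- The primary outcome is the time to the first of many components. They include eclampsia, pulmonary oedema, abruption, low platelets and raised creatinine, but also headache and oligohydramnios.
- Deliveries without progression are censored (Study outcomes; Data management and statistical considerations).
- Women who develop severe features leave further participation in the study (Study outcomes), while the primary analysis is by intention to treat.

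**The concern.** If NAC delays progression, the next question is whether pregnancies lasted longer and fewer babies were born preterm. No listed outcome addresses this. The primary hazard ratio cannot, because delivery is a censoring event in it. The low-birth-weight item is restricted to term babies and so does not register prematurity. NICU admission reflects it only indirectly.

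On the maternal side, the secondary list adds only death to safety and tolerability, and death will be too rare to compare. Hard maternal events do count in the primary composite, but only when they come first and with the same weight as softer components. An eclamptic seizure after an earlier qualifying headache adds nothing.

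A comparison of gestational age at delivery could still be made afterwards, but it would be post hoc and would carry correspondingly less weight.

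**Working it through.** **Inputs from the article (Sample size calculation).** "the total planned sample size is 153 participants", about 77 and 76 per arm; equal allocation with a two-sided alpha of 0.05; a target hazard ratio of 0.5 at 80% power; 33.3% progression at baseline; and 15% allowed for loss or missing outcomes.

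**Inputs not in the article, hence assumed.** Maternal mortality of 0.5-3% (widened to 5% as a check). SD of gestational age at delivery of 2-3 weeks (4 as a check).

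**The plan's own figure.** The stated inputs do not reproduce 153. Events needed = 4(1.960 + 0.842)²/(ln 0.5)² = 65.4, so 66. Even with 33.3% progression in both arms, 66/0.333 = 198 women, and 198/0.85 = 233. That is a separate matter. The check below takes 153 as given, and the point does not depend on it.

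**Maternal deaths, same risk m in both arms.** Expected deaths = 153m; chance of no death = (1 − m)^153.
- m = 0.5%: 0.77 deaths; chance of none 46%.
- m = 3%: 4.6 deaths; chance of none about 1%.

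**Maternal deaths, risk m on placebo and m/2 on NAC.** Expected deaths = 77m + 76m/2. Power is from Fisher's exact test at two-sided 0.05. The last column is the total needed for 80% power by the normal approximation.

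| m | Expected deaths | Chance of none | Exact power | Women needed |
|---|---|---|---|---|
| 0.5% | 0.58 | 56% | 0.0% | 18,766 |
| 1% | 1.15 | 32% | 0.01% | 9,346 |
| 2% | 2.30 | 10% | 0.2% | 4,638 |
| 3% | 3.45 | 3% | 1.0% | 3,068 |
| 5% | 5.75 | 0.3% | 4.1% | 1,812 |

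**Smallest significant split with no deaths on NAC.** Five deaths among 77 against none among 76 gives p = 0.058. Six against none gives p = 0.028.

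**Gestational age at delivery.** Evaluable women = 153 × 0.85 = 130, or 65 per arm. Detectable difference at 80% power = 2.802 × SD × √(2/65), where √(2/65) = 0.1754.
- SD 2 weeks: 0.98 weeks.
- SD 3 weeks: 1.47 weeks.
- SD 4 weeks: 1.97 weeks.

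**If women who progress are not followed to delivery.** Progression is 33.3% on placebo and, at a hazard ratio of 0.5, 1 − (1 − 0.333)^0.5 = 18.4% on NAC. About 65 × 0.667 = 43 and 65 × 0.816 = 53 women remain. Then 2.802 × SD × √(1/43 + 1/53) gives about 1.15 weeks (SD 2) to 1.7 weeks (SD 3). The loss of precision is moderate. The larger problem is that the arms would be compared after selection on an event that treatment is meant to change.

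**The case against.** The strongest case on the other side has five parts.

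1. *Maternal benefit is not ignored.* Safety and tolerability is measured in the mothers, and most of the primary composite is maternal morbidity. This stands. A reader might infer that death is the only maternal secondary outcome, or that the trial cannot show any benefit to mothers; the article supports neither. The gap concerns maternal efficacy among the secondaries, and morbidity beyond the first event.

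2. *Secondary outcomes in a proof-of-concept trial need not be powered, and deaths are normally just reported.* This stands for mortality and is why it should be descriptive. It does not explain why a recorded variable that is informative at this size is left off the list.

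3. *The objective is time to progression, and the preterm-delivery sentence describes the field.* This is partly right: the article makes no promise to test prolongation of pregnancy. But the Introduction and the Discussion both use preterm delivery to justify the need for treatment.

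4. *The article condenses a fuller protocol.* It does, but the list is numbered and its maternal item is defined in parentheses as mortality. Which outcomes exist is a choice stated here, not analysis detail deferred elsewhere.

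5. *The data may not be there.* A reader might infer that everything needed is already collected for every woman, so that the remedy needs no new data. The article does not support that: women with severe features leave further participation, so their later events and delivery data are not assured. This stands and shapes the fix.

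Two further limits apply. A new severe-morbidity composite would overlap the primary outcome and has no stated event rate, so separate reporting of components is the safer request. It also goes too far to say that neonatal results cannot be interpreted: gestational age can be tabulated by arm from the CRF without being a named outcome.

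**Conclusion.** The point holds in this limited form and should be addressed before enrolment. The one maternal efficacy secondary is uninformative at 153 women: exact power for a halving is at most about 1% at an assumed 0.5-3% mortality, and about 4% even at 5%. No prespecified outcome tests whether delayed progression lengthens pregnancy or reduces preterm birth, although a comparison of gestational age at delivery could detect about 1.0-1.5 weeks. That range rests on an assumed SD of 2-3 weeks, 15% loss, and follow-up to delivery of women who progress. The mortality conclusion holds across the whole assumed range. The gestational-age figure is more sensitive to its assumptions.

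**What to change.** In Study outcomes:

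- Add as supportive secondary outcomes, by intention to treat: gestational age at delivery, birth before 34 weeks, birth before 37 weeks, and days from randomisation to delivery.
- State that maternal deaths will be reported descriptively by arm.
- Report the hard maternal components of the primary composite (eclampsia, pulmonary oedema, placental abruption, low platelets, raised creatinine) separately by arm, also as supportive.
- Reconcile the sentence removing women with severe features from further participation with the intention-to-treat analysis and with the delivery and neonatal data in the follow-up text. Outcome data should be collected to delivery and postpartum for all randomised women. This concerns data collection only, not clinical management.

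Cost: a wording change and a registry update before enrolment (Trial status says recruitment had not begun at submission), completion of delivery records for women who progress, and a few more comparisons labelled supportive.

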
**Table 1 pone.0347695.t001:** Time and events schedule.

Study Phase	Screening	Treatment/Follow-up Phase (Gestational Age)^a^												
Week		24–34 weeks	25 weeks	26 weeks	27 weeks	28 weeks	39 weeks	30 weeks	31 weeks	32 weeks	33 weeks	34 weeks	Postpartum	End-of-Study^b^
Inclusion and exclusion criteria	X													
Informed consent (ICF)^c^	X	X												
Sociodemographic and clinical information	X	X												
Randomization		X												
Oral NAC/Placebo dispensing			X	X	X	X	X	X	X	X	X	X		
Compliance assessment^d^			X	X	X	X	X	X	X	X	X	X		
Follow-up evaluation visits				X	X	X	X	X	X	X	X	X	X	
Primary endpoint (preeclampsia with severe features)						X	X	X	X	X	X	X		
Secondary endpoints						X	X	X	X	X	X	X	X	
Assessment of serum glutathione and homocysteine						X				X			X	
CBC, Renal and Liver Function tests		X		X		X		X		X		X		
Fetal growth scans and umbilical artery velocimetry										X		X		
Postpartum outcomes (NICU admission, neonatal mortality)						X	X	X	X	X	X	X	X	X
Study close-out														X
Adverse event review^e^	Continuous review													

a. There will be a minimum of 1 week between routine follow-up visits during pregnancy.

b. End of study is defined as 4 weeks postpartum or in case of early dropout.

c. Informed consent must be signed before any study-related procedures.

d. Drug compliance will be assessed via pill count and self-report thereafter.

e. Adverse events and concomitant medications will be monitored throughout the study, from the signing of the ICF onwards, until the participant’s last study-related activity or until the participant has been deemed lost to follow-up after demonstrating due diligence in follow-up efforts.

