### Data management and statistical considerations

Data will be collected prospectively with continuous data entry and checking. Queries will be actively pursued to ensure prompt clarification. Data will be entered into the REDCap database and then exported to Stata version 18.0 for Windows (StataCorp LLC, Texas, USA) for statistical analyses. Missing or incomplete data will be handled by running a missing values analysis using pairwise or listwise deletion if no pattern is detected or the multiple imputation method if a pattern is detected [26]. The primary analysis will be conducted on an intention-to-treat basis. The effectiveness of blinding will be evaluated using descriptive statistics and by comparing the proportion of correct guesses between study arms using the Chi-square test. Kaplan-Meier estimates with a Log-rank test will be used to calculate and compare the time-to-disease progression for the treatment groups while considering deliveries without preeclampsia with severe features as censored observations. We will then perform Cox proportional hazard models with a backwards conditional method to compare the study outcomes between the treatment arms while adjusting for other covariates using hazard ratios (HRs) and 95% confidence intervals (95%CIs). We will assess the calibration or goodness-of-fit statistic of the final model using the Hosmer-Lemeshow test, while the model’s explanatory power will be reported with Nagelkerke’s pseudo-R². Subgroup analyses will also be performed to assess the differential effects of significant covariates on the impact of NAC on disease progression. With oversight from the DSMC, two interim analyses of efficacy and futility for the primary outcome (progression to severe disease) will be conducted at 50% and 75% enrolment using O’Brien-Fleming stopping criteria [27] at cutoff *p*-values of less than 0.013 and 0.025, respectively

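### Excluding women from the study once severe features develop would, read literally, end maternal, neonatal and safety follow-up in the highest-risk women, and it conflicts with the protocol's own follow-up schedule

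*Protocol article*

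**What the plan says.** The Study outcomes section lists the secondary outcomes as "1) safety and treatment tolerability, (2) maternal outcome (maternal mortality), and (3) composite neonatal outcomes". The neonatal composite includes stillbirth, NICU admission, and perinatal and neonatal mortality. The section then closes with a rule for women whose preeclampsia acquires severe features: they "will be managed as per the obstetric unit protocol and will be excluded from further participation in the study". The rule is not limited to study drug or to scheduled visits.

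Other parts of the article describe longer follow-up:

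- The Follow-up evaluations paragraph has data collection running until the trial ends or the participant withdraws. The items it records at and after delivery include "neonatal status at birth, 7th- and 28th-day (dead/alive") and NICU admission and length of stay.
- Table 1 has a row for postpartum outcomes that extends to the end of the study. Footnote b reads: "End of study is defined as 4 weeks postpartum or in case of early dropout". Footnote e ends adverse-event monitoring at the participant's last study-related activity or when she is deemed lost to follow-up.
- The statistical section says: "The primary analysis will be conducted on an intention-to-treat basis". For missing data it provides for "pairwise or listwise deletion if no pattern is detected or the multiple imputation method if a pattern is detected".

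**The concern.** The Introduction itself says that severe features carry a higher risk of adverse maternal and fetal outcomes. A rule that ends participation at that moment stops observation in the women most likely to have the secondary events, and mostly before those events can happen.

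The remaining comparison would be between women who did not reach severe features in each arm. Membership of that group is decided after randomisation and is what NAC is hypothesised to change, so randomisation no longer protects the comparison. The direction of the resulting bias cannot be known in advance.

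Safety is affected in the same way. The stopping threshold under Management of adverse events is 30% of enrolled patients with an SAE or SUSAR. If adverse-event review ends at exclusion, later serious events drop out of the numerator while the women stay in the denominator.

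**Working it through.** **Inputs.** All come from the Sample size calculation section:

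- "an estimated 33.3% baseline probability of disease progression", so control risk p0 = 0.333;
- "80% statistical power to detect a hazard ratio of 0.5 between the NAC and placebo groups", so HR = 0.5;
- 153 women allocated 1:1, so 76.5 per arm;
- a 15% allowance for loss to follow-up or missing outcome data.

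**The plan's own figure.** The plan does not state how many women the rule would remove. Its stated total of 153 is taken as given here. It does not reproduce from the stated inputs: the Schoenfeld formula gives 66 events, 66 / 0.258 = 256 women, and 256 / 0.85 = 302 after loss. That is a separate matter. It does not alter the percentages below, and the counts simply scale with the total.

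**Expected removals, if every woman who progresses is excluded.**

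- NAC risk under proportional hazards: p1 = 1 − (1 − 0.333)^0.5 = 0.183.
- Placebo: 76.5 × 0.333 = 25.5 women (33.3%).
- NAC: 76.5 × 0.183 = 14.0 women (18.3%).
- Overall: (25.5 + 14.0) / 153 = 25.8%, against the 15% allowance.
- Difference between arms: 33.3% − 18.3% = 15.0 percentage points.

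**Sensitivity.**

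| Scenario | Placebo removed | NAC removed |
|---|---|---|
| Plan's inputs, HR 0.5 | 25.5 | 14.0 |
| No treatment effect (HR 1) | 25.5 | 25.5 |
| Assumed control progression 20%, HR 0.5 | 15.3 | 8.1 |
| Assumed control progression 50%, HR 0.5 | 38.3 | 22.4 |

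Under no effect the loss is balanced in number, but it still falls on the high-risk women.

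**Share of events unseen (illustration only).** The documents give no neonatal risks by progression status. Assume a composite risk of 60% after progression and 20% otherwise, the same in both arms.

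- Placebo: 0.333 × 0.60 = 0.200 after progression and 0.667 × 0.20 = 0.133 otherwise, total 0.333. Unseen: 0.200 / 0.333 = 60%.
- NAC: 0.183 × 0.60 = 0.110 and 0.817 × 0.20 = 0.163, total 0.273. Unseen: 0.110 / 0.273 = 40%.
- With assumed risks from 50%/30% to 80%/20%, the unseen share runs from 45% to 67% on placebo and from 27% to 47% on NAC.

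**Scope of the rule.** It names preeclampsia with severe features. The progression composite in the same section is broader and includes, for example, 3+ proteinuria, fetal growth restriction and oligohydramnios. Table 1 and the statistical section use the severe-features term for the endpoint itself. Whether all women who progress are excluded is therefore unclear, and the counts are upper figures.

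**Missing-data rule.** If outcomes after progression are never recorded, deletion discards those women. Imputation has no observed outcomes after progression from which to learn. Neither recovers what was not collected.

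**The case against.** The strongest reply is that the outcomes may not be lost at all. A woman removed by rule has not withdrawn, and the follow-up paragraph collects data until termination or withdrawal. The delivery and neonatal items are not restricted to women without progression, and the study ends 4 weeks postpartum. On this view, exclusion means only no more study drug and study visits. That reading is possible, so a reader who concludes that loss is certain goes too far. But the general text does not exempt women covered by the specific rule, and footnote b also allows the study to end at early dropout. Two sites could apply the text differently.

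Several stronger readings are tempting and are not supported:

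- **That the rule breaches intention-to-treat.** The sentence covers the primary analysis only, and there the event has already been counted when the rule applies.
- **That all secondary outcomes fall at or after delivery.** Maternal death, fetal death and growth restriction can come earlier.
- **That loss is necessarily unequal between arms.** It is unequal in number only if NAC affects progression.
- **That any neonatal benefit is removed by construction.** Such a result comes from assuming equal risks in both arms within progression status.
- **That imputation would omit progression status.** The article does not say so, and the imputation model may be set out in an analysis plan that is not shown.

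It is also fair that this is a proof-of-concept trial whose secondary comparisons will be imprecise in any case. That limits the consequences but does not justify a rule that makes those comparisons unreliable.

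**Conclusion.** The point holds as a defect in a stated rule, not as a missing detail. Followed as written, the rule conditions the secondary and safety comparisons on a post-randomisation event, and it contradicts the article's own follow-up schedule. The primary endpoint is not harmed.

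The size, up to about 25 placebo and 14 NAC women, rests on three assumptions: the plan's 33.3% control progression, its hazard ratio of 0.5 with proportional hazards, and exclusion of every woman who progresses. If only some meet the severe-features criterion, fewer are removed. The share of neonatal events unseen depends on assumed risks and shows the mechanism only. The conflict between the passages depends on none of these figures.

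**What to change.** Reconcile the last sentence of the Study outcomes section with the Follow-up evaluations paragraph and Table 1 by separating the end of study treatment from the end of outcome follow-up. The text could state:

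> Reaching the primary endpoint does not end outcome data collection. Every randomised woman and her neonate are followed to the end of study at 4 weeks postpartum for all secondary and safety outcomes, and are analysed in the arm to which the woman was randomised.

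Align footnotes b and e of Table 1 with this, and say whether the rule applies to every component of the progression composite or only to severe features.

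Do not simply delete the exclusion clause. It may also be the only text that ends study drug at this point, whereas the Abstract and the randomisation section run study drug to 34 weeks or delivery. What happens to study drug and clinical management after progression is for the investigators to reconcile, and this point takes no position on it.

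The cost is a small amount of extra delivery and 28-day data collection. It includes contact with women who may deliver elsewhere, since the article does not say that all will deliver at the study hospitals. The Trial status section says recruitment had not begun at submission, so the change is cheapest if made before enrolment.
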